## Discussion

The concept of ERAS, or fast-track surgery, was introduced in 1997 by [name] [2], a gastrointestinal surgeon who won 2014 Excellence in Research Award by the ASA for his outstanding contributions to anesthesiology by the creation of ERAS. A number of studies, including clinical studies [11–13], reviews [6, 14, 15], and meta-analyses [4, 16, 17], demonstrated that compared with conventional treatment, implementation of the ERAS protocol could be associated with reduced LOS in hospital, decreased morbidity, attenuated stress, lower in-hospital cost, and accelerated recovery in various types of surgery during the perioperative period.

ERAS is a pathway involving multidisciplinary efforts including surgery, anesthesia, psychology, nutrition, and nursing support. The outcomes of the ERAS pathway are affected by multiple aspects and anesthesia is just one of them. However, anesthesia does play an important role as it impacts the short-term recovery, patient satisfaction, in-hospital complications such as the incidences of postoperative cognitive dysfunction (POCD) and PONV [18, 19], and in some cases, even long-term outcomes [20, 21]. In this study, we develop an ERAS pathway with the emphasis on minimizing the residual effects of anesthetics by using short-acting agents such as remifentanil, propofol, or desflurane so as to achieve rapid recovery. This combination regimen has been reported to facilitate early recovery without increasing PONV and pain [22]. To prevent the fast onset of postoperative pain because of the cessation of intraoperative remifentanil infusion, generous wound infiltration with 0.2% ropivacaine will be given, in order to avoid the use of long-acting opioids and facilitate early recovery.

By conducting this study, we hope to introduce the concept of ERAS to surgeons, anesthesiologists, nurses, and other allied health professionals. The ERAS pathway requires contributions from all of them. For the comparison group, there is no specific protocol regarding the conventional standard of care in each center, because we do not need to set up a standard “conventional” process to adjust their clinical practice only to make a comparison group with uniform standards. In contrast, for the ERAS group, the pathway is set up strictly with considerations of various aspects. Therefore, the implementation of this study requires deep understanding of ERAS and good collaboration among surgeons, anesthesiologists, ward nurses, and other allied health professionals.

With the hypothesis that ERAS could reduce the LOS while not increasing complications and in-hospital cost when compared with the current clinical practice, we also focus on whether the ERAS pathway could improve the patient’s quality of life or save medical resources. The outcome is to reflect these areas of interest. The primary outcome is LOS in hospital, which is affected by multiple factors such as preoperative preparation, optimization of patient’s pre-morbidities, perioperative anesthetic management, and in-hospital postoperative complications etc. It is an important index relevant to both patient’s quality of life and medical cost. In addition, hospital LOS is not only one of the most concerned outcomes by physicians, but also an index that governments of different countries are attempting to reduce in order to decrease healthcare costs [23]. Secondary outcomes including 30-day mortality, incidence of in-hospital complications, NRS for postoperative pain, total in-hospital cost, and 30-day readmission rate are all related to our hypothesis. Moreover, we divided the in-hospital complications into five grades to elaborate the severity of complications with a clear statement.

In summary, this trial is designed to test the hypothesis that the ERAS pathway could be superior to conventional clinical practice in reducing LOS without increasing the incidence of complications or medical cost.

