**Methods/Design:**

This trial is a prospective, open-labelled, multi-centered, randomized controlled trial that will test the superiority of the ERAS pathway in term of LOS in hospital for the patients undergoing primary THA or TKA compared to current non-ERAS clinical practice. A total of 640 patients undergoing primary THA or TKA will be randomly allocated to either ERAS pathway (ERAS group) or conventional care according to individual participating center (non-ERAS group). The primary outcome is the total LOS in hospital; the secondary outcomes include postoperative LOS, all-cause mortality by 30 days after operation, in-hospital complications, early mobilization, postoperative pain control, total in-hospital cost, and readmission rate by 30 days after discharge from the hospital.

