### Sample size calculation

Our primary hypothesis is that the application of the ERAS pathway would reduce the LOS in hospital when compared to the current non-ERAS practice in total joint arthroplasty (TJA). According to retrospective analysis of LOS of in hospital of TJA in 2014 (when the ERAS pathway was just proposed) and 2016 (when the ERAS pathway was applied in about 50% of patients) in the Department of Orthopedics, West China Hospital of Sichuan University, the mean LOS of THA was 10 ± 1.5 days in 2014 and 8.6 ± 1.1 days in 2016; the mean LOS of TKA was 12.1 ± 2.1 days in 2014 and 8.9 ± 1.5 days in 2017. For THA, assuming the difference between the two groups was a 5% significance level and a power of 0.90, 17 patients in each group are required; for TKA, assuming the difference between two groups was a 5% significance level and a power of 0.90, only seven patients in each group are required for a comparison within the group. Considering an estimated 20% dropout rate, there should be 42 patients in each group for THA and 20 patients in each group for TKA; a total of 62 patients are required for this study [10]. For a better application of the ERAS pathway for orthopedic surgeons and anesthesiologists, we increased the sample size to 160 individuals in each group for THA and TKA, and a total of 640 individuals will be included. We plan to enroll 320 patients undergoing TKA to participate in this trial in the first stage and enroll 320 patients undergoing THA after completion. A primary comparison will be performed separately for TKA and THA.

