### Statistical analysis

We plan to execute this trial in two stages, that is, we test the hypothesis in TKA first and then in THA, and the primary comparison will be performed separately for TKA and THA. An intent-to-treat analysis will be performed to analyze all primary and secondary outcomes by using SPSS18.0 software (Statistic Package for Social Science, SPSS, Inc., Chicago, IL, USA). The baseline continuous variables will be summarized using mean ± standard deviation or median (interquartile range) for continuous variables as appropriate. Categorical variables will be summarized using frequency (percentage).

Primary outcome: normality will be assessed for the primary outcome LOS. Appropriate transformation will be made if there is an assumption violation. We will use independent two-sample t-test to compare the LOS between the two groups. A *p* value < 5% will be considered as significant. For the primary outcome, we will also perform a sensitivity analysis using an analysis of covariance model (ANCOVA) with LOS as the response variable, the treatment group as the main factor adjusting for potentially imbalanced baseline characteristics and center effect.

For the primary outcome, we will also perform subgroup analysis based on subgroups defined by each of the age groups (< 65 years, ≥ 65 years), gender (male, female), and American Society of Anesthesiologists (ASA) class (I–II, III, or higher). Analyses will be performed for each subgroup in a similar way to the primary analysis.

For the secondary outcomes, the continuous variables (postoperative LOS, mobilization time, NRS, etc.) will be assessed for normality. Two-sample t-test or Wilcoxon rank sum test will be used for comparison depending on the normality test result. For categorical outcomes, odds ratio will be calculated and tested using Chi-square test. A *p* value < 0.05 will be considered statistically significant. We will use Kaplan–Meier plots to describe the mortality and compare the mortality at 30 days using a log rank test for fixed time points.

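### The Discussion says the trial is designed to test that ERAS does not increase complications or cost, but the planned difference tests cannot support a no-increase claim

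*Protocol article*

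**What the plan says.** The Discussion states the no-increase aim twice. It introduces the choice of outcomes with "With the hypothesis that ERAS could reduce the LOS while not increasing complications and in-hospital cost", and its closing summary says the trial is designed to test the hypothesis that the pathway "could be superior to conventional clinical practice in reducing LOS without increasing the incidence of complications or medical cost".

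The Statistical analysis section then fixes the tests for secondary outcomes:

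- Complications are categorical: "For categorical outcomes, odds ratio will be calculated and tested using Chi-square test".
- Cost is not named there, but as a continuous outcome it falls under: "Two-sample t-test or Wilcoxon rank sum test will be used for comparison depending on the normality test result".
- The criterion is that a p "value < 0.05 will be considered statistically significant".

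Elsewhere the declared aim is LOS only. The Abstract says the trial "will test the superiority of the ERAS pathway in term of LOS in hospital", and Sample size calculation says "Our primary hypothesis is that the application of the ERAS pathway would reduce the LOS in hospital". The Secondary outcomes section lists in-hospital complications and total in-hospital cost as secondary.

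**The concern.** To say that complications or cost are not increased is to make a claim of the non-inferiority kind. It needs evidence that any increase is smaller than some amount. The planned tests take no difference as their null hypothesis, so failing to reject it shows only that the data did not exclude zero. They may equally fail to exclude an increase that matters.

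The article states an aim and chooses tests that do not address it. That mismatch is visible in the published text and does not depend on what an unseen analysis plan may contain. At stake is the safety and cost half of the closing sentence of the Discussion. The primary comparison of LOS is not affected.

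**Working it through.** **1. The plan's own sample size.** Inputs from Sample size calculation: THA 10 ± 1.5 vs 8.6 ± 1.1 days; TKA 12.1 ± 2.1 vs 8.9 ± 1.5 days; alpha 5%; power 0.90. Formula: n per group = 2(z_α + z_β)²·SD²/δ², with SD² the mean of the two variances.

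- THA: SD² = (2.25 + 1.21)/2 = 1.73 and δ = 1.4. Two-sided: 2 × 10.51 × 1.73/1.96 = 18.6, so 19. One-sided gives 16. The stated 17 lies between them.
- TKA: SD² = (4.41 + 2.25)/2 = 3.33 and δ = 3.2. Two-sided: 2 × 10.51 × 3.33/10.24 = 6.8, so 7, as stated.

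Both figures come from LOS alone. The later increase to 160 per group per joint is not justified by complications or cost. At 160 per arm, power for LOS exceeds 99.9% for both joints.

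**2. Assumptions for complications and cost.** The document gives no complication rate, no cost SD and no margin, so those below are assumed. Sidedness is not stated; two-sided 5% is assumed. Using 160 per arm assumes that secondary outcomes, like the primary comparison, are analysed by joint. Pooling both joints gives 320 per arm.

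**3. Precision for complications.** With equal observed rates p, half-width = 1.96·√(2p(1−p)/n).

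- p = 10%, n = 160: 1.96 × √(0.18/160) = 1.96 × 0.0335 = 6.6 points.
- p = 20%, n = 160: 1.96 × √(0.32/160) = 1.96 × 0.0447 = 8.8 points.
- p = 10%, n = 320: 1.96 × √(0.18/320) = 1.96 × 0.0237 = 4.6 points.

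So with identical observed rates of 10%, a by-joint result would still be compatible with a rise of over 6 points.

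**4. Power of the planned chi-square test.** Power = Φ{[|p₂−p₁|√n − 1.96√(2p̄(1−p̄))] / √(p₁(1−p₁)+p₂(1−p₂))}.

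- 10% to 15%: (0.632 − 0.917)/0.466 = −0.61, power 27%.
- 20% to 30%: (1.265 − 1.200)/0.608 = 0.11, power 54%.
- 20% to 40%: (2.530 − 1.270)/0.632 = 1.99, power 98%.

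| Control rate | 1.5-fold rise, 160/arm | Doubling, 160/arm | 1.5-fold rise, 320/arm |
|---|---|---|---|
| 5% | 15% | 40% | 26% |
| 10% | 27% | 71% | 48% |
| 20% | 54% | 98% | 83% |
| 30% | 79% | about 100% | 98% |

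**5. Power for a 10% rise in mean cost, 160 per arm.** Power = Φ{0.10/(CV·√(2/160)) − 1.96}.

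- CV 0.2: Φ(4.47 − 1.96) = 99%.
- CV 0.3: Φ(2.98 − 1.96) = 85%.
- CV 0.5: Φ(1.79 − 1.96) = 43%.

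**6. If a margin were set.** With equal true rates of 10%, a 5-point margin and one-sided 0.025, power = Φ{0.05/√(0.18/n) − 1.96}.

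- n = 160: Φ(1.49 − 1.96) = 32%.
- n = 320: Φ(2.11 − 1.96) = 56%.
- 80% power needs 2 × 0.09 × (1.96 + 0.84)²/0.05², about 566 per arm.

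A 10-point margin at the same rate gives 85% power at 160 per arm.

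**The case against.** The strongest reply is that the no-increase phrase is Discussion prose. The Abstract, Background, Trial design and Sample size calculation all state a hypothesis about LOS only, and complications and cost are plainly secondary. An odds ratio is also planned, so an effect estimate will exist as well as a p value. A margin or confidence-limit rule for secondary outcomes is something an article often leaves to a fuller document.

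Much of this stands, and it limits the point. It does not remove it: the closing sentence says the trial is designed to test the no-increase claim, and the tests named for those outcomes do not test it.

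Four stronger readings are tempting, and the document does not support them:

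- **That the plan will declare no increase when p > 0.05.** No such rule is written. The Discussion wording invites that reading, but how a non-significant result will be interpreted is not stated.
- **That half of the primary hypothesis is untestable.** The primary hypothesis is LOS alone and is amply powered.
- **That the trial is underpowered for harm.** This cannot be derived without a complication rate. Grade I takes in nausea and vomiting, anxiety and insomnia, so the any-grade rate could be high, and power is good for a large rise in a common outcome or for cost with a low CV.
- **That complications and cost will be tested with 160 per arm.** Separate analysis by joint is stated only for the primary comparison.

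**Conclusion.** The point holds as a mismatch between a stated aim and the planned test. Difference tests at p < 0.05 cannot support the no-increase claim, whatever their power; even a well-powered test would need a margin or a confidence-limit rule to do so.

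The practical size depends on assumed rates, CVs and grouping. For complications at 10% to 20% and 160 per arm, increases of about 7 to 9 points would remain compatible with identical observed rates, and a 1.5-fold rise would be missed 73% (from 10%) or 46% (from 20%) of the time. At other assumed values the planned tests are sensitive: 98% power for a doubling from 20%, and 85% to 99% for a 10% cost rise at CV 0.3 to 0.2. Low power is therefore a possibility to guard against, not an established defect. The LOS comparison is unaffected.

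**What to change.** In the Discussion, state the hypothesis as superiority on LOS, with in-hospital complications and total in-hospital cost as secondary outcomes. In Statistical analysis, say that these will be reported as ERAS-minus-control differences with 95% CIs, together with odds ratios and their CIs for complications. Add that p > 0.05 will not be taken to mean no increase. This changes wording only. The cost is giving up a no-increase claim that the design cannot support.

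If the sponsor wishes to keep the claim, it should prespecify, before outcome data are compared by arm, a margin for in-hospital complications and one for mean in-hospital cost. It should conclude no unacceptable increase only if the upper 95% confidence limit lies below the margin, and say whether the joints are pooled. Complications should keep the in-hospital definition in Secondary outcomes; the 30-day windows there apply to mortality and readmission. This route has a real price: at an assumed 10% rate and a 5-point margin, power is 32% at 160 per arm and about 56% pooled at 320 per arm. That should be stated alongside the margin.

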## Trial status

The protocol version number is V2.0 and the date of this version is 26 January 2019. The anticipated starting date of recruitment is 1 August 2019. Recruitment is expected to be completed in December 2021.

## Data Availability

The individual participant data and related materials will be uploaded in the IPD sharing platform to enable data sharing and will be available after the researcher’s agreement on reasonable request.

## Abbreviations

ASA: American Society of Anesthesiologists
BIS: Bispectral Index
CRS: Central Randomization System
ERAS: Enhanced recovery after surgery
LOS: Length of stay
NRS: Numerical rating scales
PACU: Post-anesthesia care unit
POCD: Postoperative cognitive dysfunction
PONV: Postoperative nausea and vomiting
SPSS: Statistic Package for Social Science
THA: Total hip arthroplasty
TKA: Total knee arthroplasty
